## Methods and Analysis

### Setting and Participants

The study will be conducted in six clinical centers in Shanghai, China. The leading center is Shanghai Ren Ji Hospital, which is one of the main teaching hospitals of the Shanghai Jiao Tong University School of medicine. Ren Ji Hospital is also one of the biggest clinical centers of neuroimmunological disorders in China. The five branch centers are Shanghai Rui Jin Hospital, Shanghai Xin Hua Hospital, Shanghai General Hospital, Shanghai Sixth People's Hospital, and Shanghai Ninth People's Hospital. In this study protocol, only the patients who fulfilled the diagnostic criteria of NMOSD established by Wingerchuk et al. (26) will be included.

The study protocol has been approved by the Ethics Committees of Ren Ji Hospital (2016-071K).

Patients will be recruited from those neuro-immunological centers of Neurology departments in China. Eligible patients will be invited to participate. All the participants will receive adequate information about the nature, purpose, possible risk, and benefits of the trial, and about alternative therapeutic choices. A signed written informed consent form will be obtained from all the participants before enrollment.

The clinical study will be conducted in accordance with all the national regulations and complies with the principles of the World Medical Association Declaration of Helsinki—Ethical Principles for Medical Research Involving Human Subjects, with all its amendments, and also with the principles of Good Clinical Practice.

The clinical information collected including age, sex, past medical history, NMOSD attack time and frequency, corrected visual acuity by standard logarithmic visual acuity chart, Expanded Disability Status Scale (EDSS) score, Opticospinal Impairment Scale (OSIS) score, Hauser walking index, quality of life short Form-36 (SF-36) score, serum status of anti-AQP4 antibody (tested in a cell-based assay), laboratory tests as listed in Table 1, electrocardiogram, abdominal ultrasound, chest X-ray or computed tomography, optical coherence tomography, number of brain and spinal cord lesions on MR images, immunomodulatory drugs used in the past 6 months, etc.

**Table 1 T1:** Schedule of activities of human umbilical cord mesenchymal stem cells (hUC–MSCs) to treat neuromyelitis optica spectrum disorder (hUC–MSC–NMOSD) study.

**Follow-up Period**	**V0** **(Screening)**	**V1** **(Baseline)**	**V2**	**V3**	**V4**	**V5**	**V6**	**V7**	**V8**	**V9**

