### Inclusion Criteria

1) 18–75 years of age;2) Met the diagnostic criteria of NMOSD (established by the International Panel for NMOSD in 2015) (26), and serum AQP4-antibody-positive;3) In the remission phase, defined as no new or worsening of neurological symptoms and signs in the last 30 days;4) EDSS (Expanded Disability Status Scale) score ≤ 8;5) Taking azathioprine or mycophenolate mofetil as ongoing treatment for NMOSD;6) The results of the hepatic and renal function tests, complete blood count, and urinalysis are unremarkable;7) The coagulation tests are unremarkable;8) Be able to end the follow-up period;9) Signed the informed consent (by patients or their families).

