### Group Allocation, Randomization, and Blinding

The first phase of the trial is an open-label, dose-escalation study that will be performed in a leading center, the Shanghai Ren Ji Hospital. For stages 2 and 3, allocation sequences were generated by an independent statistician by permuted blocks randomization method (block sizes of four or eight). The conceal of allocation sequences were performed by using an integrated web response system (IWRS). The research physician will enroll participants and then assign participants to interventions according to allocation results from IWRS. In stage 2, there are four arms, which are the low dose group (1 × 10^6^ MSC / kg·weight), the medium dose group (2 × 10^6^ MSC / kg·weight), the high dose group (5 × 10^6^ MSC / kg·weight), and the control group (stem cell base solution). Patients will be assigned randomly in a 1:1:1:1 ratio to hUC–MSC groups and control group, respectively. In stage 3, there are two treatment arms. Patients will be assigned randomly in a 1:1 ratio to the hUC–MSC group and control group, respectively. To avoid ethical problems, we designed an add-on trial. Patients in the placebo-controlled group will receive a placebo while they already receive an established regular treatment (azathioprine or mycophenolate mofetil). Therefore, the allocation ratio of 1:1 was based on optimal statistical power and add-on trial design. In stages 2 and 3, all the participants, investigators, and statistician are blinded to group allocation until the end of the study and data analysis. Only pharmacists who are in charge of preparing study drugs are not blinded. Double-blinding will be performed *via* a centralized randomization system. Subjects who leave the study after random allocation will not be replaced.

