### Statistical Analysis

The Kolmogorov–Smirnov Z test will be used for checking data normality. Categorical variables will be summarized as counts (percentage) and continuous variables as the means (standard error, SE) or medians (interquartile ranges, IQR), if not normally distributed. For the primary endpoint of the first time of recurrence, survival analysis will be conducted to analyze between-group differences. The Kaplan–Meier estimates for time of recurrence are presented for all groups. Hazard ratios for the comparison of between groups and 95% CIs were calculated with the Cox proportional-hazards model. Prespecified subgroup analyses of the primary outcome were stratified by, EDSS score at baseline, disease duration, age at randomization, the total number of previous relapses, number of relapses 2 years before randomization, and regular treatment. For secondary outcomes, statistical comparisons between the groups will be performed using Student's *t*-test or the Mann–Whitney U test for continuous variables, as well as the chi-square and Fisher's exact tests for categorical variables, as deemed appropriate. Correlations between continuous variables will be assessed by Pearson's correlation coefficient or Spearman's correlation coefficient. All missing data were not imputed in this study.

In this study, two analysis sets will be required. For the safety set (SS) analysis, all safety indicators will be obtained from those who have undergone at least one dose of hUC–MSC infusions. For the effectiveness analysis set, the intention to treat (ITT) analysis set will be used.

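### Background drug and prior relapses are recorded and named as subgroups, but no stratum or covariate is named for randomisation or the primary Cox comparison: valid, but a modest loss of efficiency if they are prognostic

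*Protocol article*

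**What the plan says.** All references are to the protocol article.

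- **Inclusion Criteria.** Either background drug qualifies: "Taking azathioprine or mycophenolate mofetil as ongoing treatment for NMOSD". The only limit on relapse history is "In the remission phase, defined as no new or worsening of neurological symptoms and signs in the last 30 days".
- **Setting and Participants.** Both factors are recorded at baseline: "NMOSD attack time and frequency" and "immunomodulatory drugs used in the past 6 months".
- **Group Allocation, Randomization, and Blinding.** The treatment is given on top of the background drug: "To avoid ethical problems, we designed an add-on trial". For stages 2 and 3 the lists come from a "permuted blocks randomization method (block sizes of four or eight"), run through a web response system. No stratification factor is named.
- **Statistical Analysis.** The primary effect estimate is described as follows: "Hazard ratios for the comparison of between groups and 95% CIs were calculated with the Cox proportional-hazards model". No covariate or stratum is named. The list of prespecified subgroups for the primary outcome includes total previous relapses and ends with "number of relapses 2 years before randomization, and regular treatment".
- **Study Design.** Stage 2 has four arms of 40 and stage 3 has two arms of 160.

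**The concern.** By listing regular treatment and prior relapses as subgroups, the authors treat them as relevant to the primary outcome. As described, though, the factors only split the data. They neither balance the arms nor sharpen the main estimate.

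Two things follow if they predict relapse. First, a Cox model that omits prognostic factors estimates a hazard ratio closer to 1 than the effect within patients of the same risk, and its test loses power. Second, stage 2 compares three doses with 40 patients per arm. At that size a dose can look somewhat better or worse because of who was allocated to it, and stage 2 data also enter the final inverse normal combination test.

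**Working it through.** **1. The plan's own figure.** Inputs from Sample Size Estimation: relapse 55% against 40%, two-sided 5%, 80% power, 20% loss, total 400 for stages 2 and 3.

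- Implied hazard ratio under exponential times: ln(0.60)/ln(0.45) = 0.640.
- Schoenfeld events: 4 × (1.960 + 0.842)² / (ln 0.640)² ≈ 158.
- Mean event proportion: (0.55 + 0.40)/2 = 0.475, so 158/0.475 ≈ 333 patients.
- With a 1.2 inflation: 333 × 1.2 ≈ 399, which matches 400.

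So 0.640 is a fair reading of the effect the trial is sized for.

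**2. Effect on the hazard ratio and power.** The documents give no prognostic effects, no drug split and no distribution of relapse history, so these are assumptions: background drug split 50:50; relapse history as a standardised continuous score; exponential hazard 0.7985 per year, which is −ln(0.45); true hazard ratio 0.64; 24 months of follow-up; 20% loss. Each simulated trial was analysed with and without the two factors. Results are subject to simulation error of a point or two.

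| Assumed prognostic HR (drug; relapse history per SD) | Unadjusted HR | n = 320: power unadjusted / adjusted | n = 400: power unadjusted / adjusted |
|---|---|---|---|
| 1.3; 1.3 | about 0.65 | 86% / 89% | 93% / 95% |
| 1.5; 1.6 | about 0.67 | 82% / 90% | 90% / 95% |

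With no prognostic effect, power at 320 is 89% either way. The two sizes are stage 3 alone (Study Design) and the total in Sample Size Estimation. Power exceeds the planned 80% because 24 months yield more relapses than the one-year rates used for sizing.

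A second simulation used two binary factors at 50% prevalence and 200 per arm, with a wider range of effects:

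| Assumed prognostic HR (relapse history; drug) | Unadjusted HR | Power unadjusted / adjusted |
|---|---|---|
| 1; 1 | 0.642 | 95% / 95% |
| 1.5; 1.2 | 0.647 | 94% / 95% |
| 2; 1.5 | 0.657 | 92% / 95% |
| 3; 1.5 | 0.680 | 87% / 95% |
| 4; 2 | 0.705 | 79% / 94% |

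**3. Chance imbalance.** For a factor with an assumed 50:50 split and n per arm, the SD of the difference between two arms is √(2 × 0.25/n).

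- n = 40: √(0.5/40) = 0.112. P(difference over 15 points) = 2 × [1 − Φ(0.15/0.112)] ≈ 18% per pair.
- n = 160: SD 0.056. The same probability is about 0.7%.

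**4. What an imbalance does to a stage 2 comparison.** A 15-point imbalance in a factor with hazard ratio 1.5 moves the log hazard ratio by 0.15 × ln 1.5 = 0.061. With about 52 events per pair of arms, the standard error is about 2/√52 = 0.28. The shift is therefore roughly a fifth of ordinary sampling error (0.061/0.28 = 0.22).

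**5. Dose selection.** Assumed dose hazard ratios are 0.9, 0.8 and 0.64, with 40 per arm and the lowest estimated hazard ratio selected. The chance of picking the best dose, with the same binary factors as in the second table, is:

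| Assumed prognostic HR (relapse history; drug) | Unadjusted | Adjusted | Stratified and adjusted |
|---|---|---|---|
| 1; 1 | 75% | 75% | 74% |
| 2; 1.5 | 70% | 73% | 74% |
| 3; 1.5 | 70% | 74% | 73% |
| 4; 2 | 64% | 71% | 72% |

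**The case against.** The strongest objection is that the article is silent on covariates; it does not state an unadjusted model. A covariate list may sit in the SAP, which is not at hand, and a journal article condenses. This stands as a limit on the Cox part: it cannot be said that the trial will analyse without adjustment. It carries less weight for randomisation. That section gives block sizes, the system, the ratios and who is unblinded, so a stratum would be expected there, and a later analysis plan cannot add one to lists already in use.

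Second, nothing here is invalid. Permuted blocks with an unadjusted Cox comparison is a sound intention-to-treat analysis. Chance imbalance adds noise and does not bias the test. This stands in full.

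Third, the stage 2 exposure is small against ordinary sampling error, and Study Design selects the dose on a trade-off of efficacy and toxicity without saying that the hazard ratio decides. This also stands: the gain in correct selection is about 3 to 8 points, and only under strong assumed effects.

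Two stronger readings are tempting. A reader might infer that the enrolled patients have very different relapse histories, or that these two factors are the strongest predictors of relapse. The article shows only that eligibility is open; it gives no distribution and no prognostic effect. A reader might also infer that the trial becomes underpowered. A drop from about 80% to 69% does appear if 240 patients are assumed, but the article states no such size. At 320 or 400, unadjusted power stays above 80% for the assumed effects in the first table. It falls just below, to 79%, only for the strongest pair in the second.

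**Conclusion.** The point holds as a modest efficiency gain that the plan as described leaves unused, not as an error. With assumed prognostic hazard ratios between 1.3 and 1.6, the unadjusted estimate moves from 0.64 to about 0.65 to 0.67. The power given up is about 3 to 8 points at 320 patients and 2 to 5 points at 400. The gain could be larger only with strong effects, for which the documents offer no evidence. When the factors do not matter, adjustment costs essentially nothing. Chance imbalance is a stage 2 matter; at 160 per arm it is minor. The randomisation part is the firmer of the two, because the Cox part rests on what the article does not mention.

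**What to change.** 1. **Statistical Analysis.** Prespecify, before unblinding, that the primary Cox model is stratified by regular treatment (azathioprine or mycophenolate mofetil) and adjusted for the number of relapses in the 2 years before randomisation. Stratify any accompanying log-rank test by regular treatment too. If the SAP already says this, the article needs only one sentence to that effect.
2. **Stage 2 dose selection.** Use the same adjusted estimate for the efficacy part of the trade-off.
3. **Group Allocation, Randomization, and Blinding.** Stratify by regular treatment any allocation list not yet in use, at least for stage 3. The article says sequences were already generated, so if the stage 2 lists are running, make the model change alone.

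The cost is one stratum in the web response system and a sentence or two of text. Attack frequency and recent immunomodulatory drugs are already recorded at baseline. The downside is slightly more complex reporting.

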The first stage of the trial, which will last 24 months, is an open-labeled study and will be carried out in the leading center only. The first stage aims to evaluate the safety of the infusion of hUC–MSC in NMOSD patients. Patients (*n* = 30) will be treated with three different doses of hUC–MSC. According to the process of enrollment, the first to the tenth participant is in the low-dose group (*n* = 10, 1 × 10^6^ MSC / kg·weight); the eleventh to the twentieth participant is in the medium-dose group (*n* = 10, 2 × 10^6^ MSC / kg·weight); the twenty-first to the thirtieth participant are in the high-dose group (*n* = 10, 5 × 10^6^ MSC / kg·weight). The study starts from the low dose. Only when the lower dose group ends the observation period of 3 months, the study will proceed to a higher dose group. In case of unacceptable toxic reaction occurs in the dose escalation, the study will be ended immediately. In relation to safety considerations, before enrolling the patients in the low-dose group, we will give a single medium dose of hUC–MSC to one patient and follow-up the therapy for one year. The outcome of this dosage will be used only for safety evaluation, not to evaluate the therapy's effectiveness.The second and third stages of the study protocol are part of the multi-center double-blinded randomized clinical trial. The second stage, which aims to screen out the optimal dosage, will last for 24 months and will be carried out in six centers (one leading center and five branch centers). Patients (*n* = 160) will be randomized into four groups: the low-, medium-, high-dose groups, and the controlled group (*n* = 40, respectively). In the second stage, we were seeking to determine the ‘optimal biological dose.’ The dose that allows reaching the optimal efficacy-toxicity trade-off is further selected and recommended to stage 3. The third stage, which aims to evaluate the effectiveness, will last for 24 months and will be developed in six centers. Patients (*n* = 320) will be randomized into two groups: the optimal dose group (*n* = 160) and the controlled group (*n* = 160). The third stage aims to evaluate the effectiveness and safety of hUC–MSC for NMOSD patients. The study flow chart is shown in Figure 1.

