### Sample Size Estimation

Based on previous epidemiology studies on NMOSD among Asians, the replacing rate for the patients in the first year of the onset event is estimated at 55% (27). In this study, we expected that the relapsing rate could be reduced to 40% in the MSC group, according to our preliminary data. In the first stage of an exploratory study, each dosage cohort will include 10 patients to meet the safety evaluation goal, which are 30 patients in total. In the adaptive design stages 2 and 3, a total sample size of 400 patients would have 80% power to detect 15% relapsing rate reduction at a two-sided 5% significant level, with a 20% expected loss to follow-up rate. Therefore, we expected to enroll a total number of 430 subjects in this study. The sample size of this study was determined according to the stage of trial by R software (Version 4.0.3).

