Lan–DeMets alpha-spending function with an O'Brien–Fleming boundary will be used to control the family-wise of type I error. Inverse normal combination test will be used to combine data from stages 2 and 3 in the final analysis. An independent Data and Safety Monitoring Board (DSMB) will review and evaluate the accumulated study data for participant safety, study conduct, and progress at each stage of the study. Only members of DSMB could have access to the data and results of the analysis. The Ethics Committee will be notified of any amendment to the study protocol. DSMB can make recommendations to terminate the study based on one of the following conditions: a significant difference in terms of effectiveness between groups; a significant risk-benefit ratio in one group; low degree of success in a reasonable period (such as poor compliance, low incidence of endpoint events). The advice of the DSMB meeting will be shared with the steering committee of the trial.

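### The effect size is an ordinary Cox hazard ratio with no stated link to the stage 2 dose selection or the combination test; if stage 2 patients enter it, it leans modestly towards benefit.

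*Protocol article*

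**What the plan says.** Three statements in the protocol article bear on this.

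- **Dose choice (Study Design).** In stage 2, 160 patients "will be randomized into four groups: the low-, medium-, high-dose groups, and the controlled group", 40 in each. Then: "The dose that allows reaching the optimal efficacy-toxicity trade-off is further selected and recommended to stage 3". Efficacy is therefore one of two stated criteria. No numerical rule is given.
- **Final test (Statistical Analysis).** "Inverse normal combination test will be used to combine data from stages 2 and 3 in the final analysis". A Lan-DeMets spending function with an O'Brien-Fleming boundary is also named.
- **Effect size (Statistical Analysis).** "Hazard ratios for the comparison of between groups and 95% CIs were calculated with the Cox proportional-hazards model". The section does not say whether this model is fitted to stages 2 and 3 together, to each stage, or to stage 3 alone. It also does not connect the interval to the dose selection, the combination test or the boundary.

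The Sample Size Estimation section treats stages 2 and 3 as one adaptive design: "a total sample size of 400 patients would have 80% power to detect 15% relapsing rate reduction at a two-sided 5% significant level".

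**The concern.** A dose that looks good in stage 2 is more likely to be carried forward when chance has favoured it. Reusing its stage 2 patients in the final hazard ratio carries that chance gain into the reported effect. Controlling the error rate of the test does not remove this, because estimation is a separate matter. An ordinary Cox 95% interval is also not the interval that belongs to an inverse normal combination test after selection.

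The Conclusion section expects the results to inform guideline revisions. Readers will then use the size of the hazard ratio as well as its significance.

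**Working it through.** **1. Inputs from the article.** Control relapse risk: "in the first year of the onset event is estimated at 55" per cent. Treated: "we expected that the relapsing rate could be reduced to 40% in the MSC group". Losses: "with a 20% expected loss to follow-up rate". Stage 2 has 40 per arm. Stage 3 has 160 per arm as written.

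**2. Reproducing the 400.**
- Implied hazard ratio with exponential times: ln 0.60 / ln 0.45 = 0.640.
- Events (Schoenfeld): 4 × (1.960 + 0.842)² / (ln 0.640)² = 157.3, so 158.
- Patients: 158 / 0.475 = 332.6, so 333, where 0.475 is the mean of 0.55 and 0.40.
- Losses: 333 × 1.2 = 399.6, so 400. (Dividing by 0.8 would give 416.)

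The figure is reproduced as a single two-arm comparison across stages 2 and 3. This points towards a pooled estimate but does not state one.

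**3. Head count.** Study Design gives 30 + 160 + 320 = 510, while Sample Size Estimation gives 430. The two agree if the 320 includes 80 stage 2 patients (40 selected dose, 40 control): 30 + 160 + 240 = 430, with 120 new patients per arm in stage 3. This is an inference. On that reading, even a comparison of 160 with 160 contains patients used to choose the dose. Both 160 and 120 new patients per arm are carried below.

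**4. Size of the bias by hand, worst case.** Assume that all three doses have a true hazard ratio of 0.640 and that the lowest stage 2 hazard ratio is chosen. The three contrasts share a control, so selection acts on the treated arms. The expected minimum of three independent standard normals is −3/(2√π) = −0.846. The standard deviation for an arm is 1/√(events), and stage 2 contributes a share of 40/(40 + n₃).
- Two years, 20% lost: events 40 × (1 − 0.60²) × 0.8 = 20.5, SD 0.221, stage 2 bias in log HR −0.846 × 0.221 = −0.187. With n₃ = 160 the share is 0.20, so the pooled bias is −0.037 and the HR 0.640 × exp(−0.037) = 0.616.
- One year, 20% lost: events 40 × 0.40 × 0.8 = 12.8, SD 0.280, stage 2 bias −0.237. With n₃ = 120 the share is 0.25, so the pooled bias is −0.059 and the HR 0.603.

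**5. Patient-level simulation.** 6,000 trials per scenario, exponential times, 20% dropout, no early stopping, true HR 0.640 for every dose, lowest stage 2 HR chosen:

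| New per arm, stage 3 | Follow-up | Pooled HR, by hand | Pooled HR, simulated | Upper limit below truth | Lower limit above truth | Coverage |
|---|---|---|---|---|---|---|
| 160 | 2 years | 0.616 | 0.616 | 4.3% | 1.0% | 94.7% |
| 160 | 1 year | 0.610 | 0.610 | 4.1% | 1.0% | 94.9% |
| 120 | 2 years | 0.611 | 0.611 | 4.4% | 0.9% | 94.7% |
| 120 | 1 year | 0.603 | 0.603 | 4.6% | 0.8% | 94.6% |

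Other scenarios:
- No effect at any dose: pooled HR 0.954 to 0.973 instead of 1.00.
- Unequal doses (0.90, 0.75, 0.64): pooled HR 2.3% too low (160 per arm, 2 years) and 4.5% too low (120 per arm, 1 year), against 3.8% and 5.7% with equal doses.
- Dose chosen without regard to efficacy: pooled HR 0.640, no bias.
- Stage 3 patients alone, all scenarios: bias in log HR between −0.006 and +0.003, coverage 94.5 to 95.5%.
- Ordinary Cox interval against the unadjusted combination test (both at 1.96, no interim look): they disagree on significance in 0.2 to 0.8% of trials.

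**6. Price of using stage 3 alone.** With 160 per arm the standard error is 0.139 against 0.125 pooled, a ratio of 1.11. With 120 per arm the ratio is √(160/120) = 1.15. In a normal approximation with 160 per arm and HR 0.64, the root mean squared error is about 0.126 pooled and 0.139 for stage 3 alone.

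**The case against.** The strongest reply is that the article never plans a pooled hazard ratio. Stage 3 is given the task of evaluating effectiveness, an inverse normal test combines stage-wise statistics without needing one pooled Cox fit, and a stage 3 hazard ratio is unbiased. A condensed article may also leave the estimator's details to a fuller document. This stands to the extent that the fault is conditional. What remains is that the article does fix the estimator and the test, and the two are not tied together.

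Selection is on efficacy and toxicity, so the simulated figures are an upper range for selection bias. That also stands. Stopping early for effectiveness, which the data monitoring text allows, would add bias that is not counted here.

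Pooling is also more precise: under worst-case selection its root mean squared error is still the smaller. With 160 per arm, a stage 3-only interval would disagree with the unadjusted combination test in about 8% of trials at HR 0.64 and 20% at HR 0.80. This is a good reason not to make stage 3 alone the only headline.

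A reader might go on to infer three stronger things that the documents and figures do not support:
- **The reported benefit will be overstated.** This holds only if stage 2 patients enter the model and efficacy drives the choice.
- **The Cox interval and the test conflict.** They almost never do (0.2 to 0.8% of trials).
- **Secondary endpoints are biased to the same degree.** The article does not say that they are pooled over stages. Any carry-over depends on how closely each endpoint correlates with the selection criterion, and this was not examined.

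**Conclusion.** The point holds in conditional form. If stage 2 patients enter the Cox model, the hazard ratio is biased modestly towards benefit: at a true 0.64, by 4 to 6% at worst. The ordinary interval keeps about 95% coverage, but its misses are lopsided, with 4.1 to 4.6% on the favourable side and 0.8 to 1.0% on the other. These figures assume exponential relapse times, proportional hazards, one or two years of follow-up, 20% dropout, no early stopping, equally effective doses and selection on efficacy alone. The direction of the bias is certain once efficacy influences the choice. Its size is small, and the remedy is cheap enough to be worth adopting.

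**What to change.** In the Statistical Analysis section, or in the SAP before any stage 2 comparison is unblinded:

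1. State which stages and patients the primary hazard ratio uses.
2. Obtain the 95% interval for the combined claim by inverting the same selection-adjusted combination test that supports the claim.
3. Report beside it the Cox hazard ratio from newly randomised stage 3 patients and their concurrent controls, described as the estimate free of selection bias.
4. Show the stage 2 hazard ratios for all three doses, labelled as used for selection.

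The cost is wording, slightly more analysis work and a somewhat less favourable interval. The stage 3-only estimate has a standard error about 11% larger with 160 new patients per arm, or 15% larger with 120. No additional patients or procedures are needed.

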#### Transfusion of hUC–MSCs

Subjects in the intervention groups will receive four hUC–MSC infusions every 3 months besides the primary drugs. The dosages are 1, 2, or 5 × 10^6^ MSCs per kg of body weight. The hUC–MSCs will be infused *via* the subjects' peripheral veins. The drip rate is 30 drops per min in the first 15 min of infusion and 45 drops per min in the next 15 min. If there are no adverse effects, the drip rate can be gradually increased, but never exceed 70 drops per min. The time of infusion should last no more than 1 h. After the infusion of MSCs, subjects will be infused with 500 ml normal saline.

Subjects in the control group will receive four stem cell base solution infusions (the same packaging bag as hUC–MSCs) every 3 months besides the primary drugs.

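### The safety set as defined contains no control patients, so hUC-MSC cannot be compared with control on safety within it

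*Protocol article*

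**What the plan says.** The Statistical Analysis section of the protocol article states: "In this study, two analysis sets will be required". It then fixes the use of each.

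- Safety set: "all safety indicators will be obtained from those who have undergone at least one dose of hUC–MSC infusions".
- Effectiveness: "For the effectiveness analysis set, the intention to treat (ITT) analysis set will be used".

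The section on transfusion says what the comparison arm is given: "Subjects in the control group will receive four stem cell base solution infusions". Study Design sets the stage 2 arms as "the low-, medium-, high-dose groups, and the controlled group (*n* = 40, respectively") and the stage 3 arms as "the optimal dose group (*n* = 160) and the controlled group (*n* = 160"). It also gives stage 3 a safety purpose: "The third stage aims to evaluate the effectiveness and safety of hUC–MSC for NMOSD patients".

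The Follow-Up section has side effects assessed in every participant at baseline and three-monthly. Table 1 schedules adverse event recording from V1 to V9, and its study-treatment row covers placebo as well as cells.

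**The concern.** A safety set is normally defined by exposure to any study treatment, so that the control arm supplies the background rate. Here it is defined by exposure to the active product alone. The definition would suit stage 1, which has no control arm, but the text applies it to the whole study.

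The background rate matters in this trial. Every patient must be taking azathioprine or mycophenolate mofetil, and controls also have four infusions. Infections, abnormal laboratory results and reactions around an infusion may therefore occur without any effect of the cells. If the rule is followed literally, the stage 3 safety analysis is a one-arm description, and an excess over control cannot be read from it. The randomised control arm would then add nothing to the safety results, although its data will have been collected.

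**Working it through.** The point rests on a definition, and the plan gives no figure to reproduce. The check is to match the definition to what each arm receives and to count who falls outside.

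**1. Who qualifies.** Entry requires at least one hUC-MSC infusion (Statistical Analysis). No other section defines a safety population.

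**2. Who receives hUC-MSC.** All stage 1 patients, the three dose arms of stage 2 and the selected-dose arm of stage 3. The controls of stages 2 and 3 receive base solution (Study Design; Transfusion of hUC–MSCs; Group Allocation, Randomization, and Blinding). A control could enter the set only by being given cells in error.

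**3. Count on the Study Design arm sizes.**
- hUC-MSC, randomised: 3 × 40 + 160 = 280
- Control: 40 + 160 = 200
- Total randomised: 280 + 200 = 480
- Outside the safety set: 200 / 480 = 41.7%, which is every control

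**4. Count on the other total in the article.** Sample Size Estimation gives 400 for stages 2 and 3 together, not 480. That mismatch is a separate matter, but the count should be shown both ways. Keeping stage 2 at 160 leaves 400 − 160 = 240 for stage 3. Splitting these 1:1 gives 120 per arm (an assumption, since the article does not state it).
- hUC-MSC: 120 + 120 = 240
- Control: 40 + 120 = 160
- Outside the safety set: 160 / 400 = 40%, again every control

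**5. Randomised patients in the safety set, as written and as corrected** (upper limits, taking every randomised patient to have at least one infusion as allocated).

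| Basis | As written: hUC-MSC / control | Any study infusion: hUC-MSC / control |
|---|---|---|
| 480 randomised | 280 / 0 | 280 / 200 |
| 400 randomised | 240 / 0 | 240 / 160 |

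**6. Against the stated aim and the data collection.** Stage 3 randomises 1:1 against control and is meant to evaluate safety as well as effectiveness. Side effects are to be assessed in all participants. The safety set then omits one of the two arms. These three statements do not fit together.

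**The case against.** The strongest reply is that this is loose drafting. The article uses MSC infusion as shorthand elsewhere: the discontinuation criteria speak only of intolerance to MSC infusion, although stages 2 and 3 are blinded and controls are infused too. The authors may well have meant any study infusion. That is plausible, but it does not remove the need for correction. The sentence states a rule for all safety indicators, and the only other set is reserved for effectiveness. An analysis plan, which is not shown, could define the set properly, but it would then contradict the published text.

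Other objections limit how far the point reaches, and they stand.

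- A reader might infer that no randomised safety comparison of any kind is left. That is not so. The three hUC-MSC arms of stage 2 are all inside the set and can be compared with one another.
- A reader might infer that stage 2 dose selection fails. The trade-off between efficacy and toxicity is a choice among hUC-MSC doses, and relative toxicity between doses can be judged within the set. Control rates would help, but the article does not make the choice depend on them.
- A reader might infer that the monitoring board could not act on its criterion of "a significant risk-benefit ratio in one group". The article has the board review accumulated study data and does not tie that review to the safety set.
- A reader might infer that control safety information is lost. It is collected, so the fault lies in the analysis set and not in the data.
- The article mentions dexamethasone before, and saline after, only in connection with the cells. It therefore does not establish that controls share every element of the infusion procedure, and the point does not rely on that.

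**Conclusion.** The point holds in a limited form. Followed literally, the safety set includes no control treated as allocated: 200 of 480 randomised patients on the Study Design arm sizes, or 160 of 400 if the sample size total applies and stage 3 is 240 split 1:1. The choice between the two totals changes the count but not the conclusion, because the control side is empty in both. A randomised safety comparison of hUC-MSC with control cannot be made within the defined set, which contradicts the stage 3 aim.

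The documents do not support the stronger conclusion that the trial cannot answer its safety question. The control data will exist, and a corrected definition makes the comparison available. No precision figure is attached, because the defect is one of definition and the article gives no adverse event rate from which to calculate one.

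**What to change.** Replace the safety set sentence with a definition covering all patients who received at least one infusion of study product, whether hUC-MSC or base solution, analysed by the product and dose actually received. For stages 2 and 3, report adverse event risks by arm, with differences from control and 95% confidence intervals. Report stage 1 separately and label it uncontrolled, so that its patients are not mixed into the randomised comparison.

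The cost is a sentence or two in the protocol and the matching text in the analysis plan. No extra visits, tests or patients are needed, since Table 1 already schedules the data. The change should be made and dated before unblinding. Trial Quality Assurance says that the protocol will not be amended unless a serious adverse event occurs, so the sponsor should settle where the correction is recorded and make sure that protocol and analysis plan agree.
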